(c). To assess the amount of sodium transferred to the patient or withdrawn from the patient during conventional hemodialysis, UCR and UTR. The amount of sodium removed during hemodialysis is a function of the ultrafiltration volume, the effective diffusion gradient for sodium, and diffusive sodium clearance. The effective diffusion gradient depends on the plasma water - dialysate sodium (DNa) difference, and the Gibbs-Donnan coefficient, the latter being a function of the plasma protein concentration but also being influenced by other ions in the dialysate [39,40]. The assumption that sodium removal by ultrafiltration is equal to the plasma water sodium concentration, multiplied by the ultrafiltration volume, is a simplification [41,42]. Electrolyte balances may also be influenced by the membrane charge [43]. Therefore, the amount of sodium transferred will be measured on the dialysate side. Sodium transfer will be calculated from the difference between the mean sodium concentration in partially collected, used dialysate and the fresh DNa concentration, multiplied by the total amount of dialysate used. Results will be compared to a two-pool sodium model and parameters of the model will be adjusted using the measured transfer data. The above described method is not applicable to the UCR group because the sodium concentration of fresh dialysate is not kept constant during treatment. In order to establish the model, we will measure at least ten patients during three hemodialysis sessions, and due to the formerly stated, we can only use the dialysate from patients in the conventional hemodialysis group and in the UTR group. However, after having established this model, sodium transfer for all patients - conventional, UTR, and UCR - can be calculated using this very model. The amount of sodium transferred to or withdrawn from the patient will be calculated for each patient, according to the model established in the way stated here above. The secondary outcome measure for objective (d), for example, the sodium transferred in both groups, UCR and UTR, will be compared against the conventional hemodialysis group, and afterward against one another, using the two-sided Student’s *t* test.

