Withdrawal of antihypertensives, in order to reach lower dry weight, may, to some dialysis care takers, seem unethical. However, blood pressure treatment in hemodialysis patients is highly controversial. Although blood pressure control may be the most extensively studied area in dialysis research, widely accepted propositions for the treatment of hypertension are still missing [55,56], mainly because epidemiologic studies have failed to incriminate hypertension as a cardiovascular risk factor [57]. Oral pharmacotherapy has recently been shown to yield some mortality benefit [58,59], but data from single centers in Uruguay [60], United Kingdom [61], Turkey [62] and Tassin, France [63] have consistently demonstrated that strict volume control with relatively low postdialysis dry weight targets can fully normalize the blood pressure in a great majority of hemodialysis patients. In fact, hypertension control without antihypertensive medication is actually the strongest predictor of survival in hemodialysis patients [64].

Therefore, it is ethical to withdraw antihypertensives in order to reach the adequate dry weight target, and this approach has been used before, in the DRIP trial, which did not include patients based on bioimpedance-based detection of fluid overload, but based on hypertension [11]. The mortality risk for the hemodialysis population - in observational studies - does not begin to rise before very high SBP values of 200 mmHg are reached [65,66]. However, we intend not to generally accept that the SBP during the course of the patient’s antihypertensives withdrawal phase surpasses 200 mmHg.

We have recently shown that higher DNa prescriptions are associated with IDWG, but not with worse outcomes, and that predialysis serum sodium concentrations correlate inversely with mortality risk [49,67]. Among secondary outcome parameters, principal emphasis will be placed on a measurement of intradialytic sodium balance (listed as secondary objective (c)). This analysis is necessary, as there is only one previous publication, which estimated, but did not measure sodium transfer through positive dialysate-to-serum sodium gradients [68]. The results of our investigation may help dialysis physicians in their decision concerning the dialysate sodium prescription, because they will be able to anticipate which amount of sodium is transferred during hemodialysis.

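### Sodium transfer in UCR is model output calibrated only on the other two arms, and the planned t test leaves calibration error out of both UCR contrasts

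*Protocol article*

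**What the plan says.** All of this is in the protocol article.

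- **Objectives and outcome measures, objective (c).** Transfer is to be measured on the dialysate side, from the mean sodium of partially collected used dialysate minus the fresh concentration, times dialysate volume. For one arm this fails: "The above described method is not applicable to the UCR group because the sodium concentration of fresh dialysate is not kept constant during treatment".
- **Calibration (same section).** The measurements feed a two-pool model: "parameters of the model will be adjusted using the measured transfer data". The sample is small, "we will measure at least ten patients during three hemodialysis sessions", and comes from two arms: "we can only use the dialysate from patients in the conventional hemodialysis group and in the UTR group".
- **Application (same section).** Once the model is established, "sodium transfer for all patients - conventional, UTR, and UCR - can be calculated using this very model".
- **Comparison (same section).** "the sodium transferred in both groups, UCR and UTR, will be compared against the conventional hemodialysis group, and afterward against one another", by two-sided Student's t test. The section Superiority definition sets alpha at 0.05.
- **UCR and UTR versus conventional hemodialysis.** Changing dialysate sodium during the session is part of what UCR does.
- **Discussion.** Among the secondary outcomes, "principal emphasis will be placed on a measurement of intradialytic sodium balance". The one earlier publication is faulted for having estimated sodium transfer without measuring it.
- **Statistical analysis plan.** All secondary analyses are exploratory.

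**The concern.** A two-sample t test builds its standard error from the spread between patients of the values it is given. When those values come from a fitted model, the fitted parameters carry error of their own. That error is common to every patient whose value is calculated, so enrolling more patients does not average it out, and the t test does not see it.

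In the UTR versus conventional contrast this matters little. Both arms supply calibration data and both run at constant dialysate sodium, so an error in a parameter moves both means by about the same amount. UCR differs from them in dialysate sodium, and the article itself names the difference between plasma water and dialysate sodium as a driver of transfer. An error in how the model responds to that driver can therefore move the UCR mean and not the others. Two of the three planned contrasts involve UCR.

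At stake is how firmly those two results can be stated. The Discussion puts this outcome first among the secondary ones, calls it a measurement, and hopes it will inform dialysate sodium prescription. For UCR the trial will also have estimated and not measured.

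**Working it through.** **1. Arm size.** No sample size is given for sodium, so the sodium tests inherit the primary endpoint's arms. With difference 10%, SD 10%, two-sided alpha 0.05 and beta 0.2, the normal approximation gives 2 × (1.960 + 0.842)² × (10/10)² = 15.7, so 16 per group. The exact t test gives 16.7, so 17 (power 0.807), which is the plan's figure. With 10% dropout, 17/0.9 = 18.9, so 19 per group or 57 in all. The plan sets 60, which at 1:1:1 is 20 per arm.

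**2. Type I error when calibration error is left out.** Let the between-patient SD be 1, with n per arm. The t test uses SE = √(2/n). Let *c* be the standard error that calibration adds to the contrast, in between-patient SDs. The true SE is then √(2/n + c²), which exceeds the t-test SE by the factor R = √(1 + c²/(2/n)). The real two-sided type I error is the probability that a t variable with 2n − 2 degrees of freedom exceeds the critical value divided by R. The documents do not give *c*, so the values below are assumptions.

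| c | R, n = 20 | Type I error, n = 20 | Type I error, n = 17 |
|---|---|---|---|
| 0 | 1.00 | 5.0% | 5.0% |
| 0.1 | √(1 + 0.01/0.1) = 1.05 | 6.1% | 5.9% |
| 0.2 | √(1 + 0.04/0.1) = 1.18 | 9.5% | 8.8% |
| 0.316 | √(1 + 0.1/0.1) = 1.41 | 16.0% | 14.4% |

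**3. Which contrasts are affected.** A simulation used a linear stand-in for the two-pool model: transfer = a + g + e, where the driver g has SD 1 in each arm and e is a patient-level residual. Intercept and slope were fitted on ten patients, taken as five conventional and five UTR, then applied to 20 per arm (4,000 runs per setting). The shift is the amount by which the mean driver in UCR differs from the calibration arms. Entries are the coverage of the nominal 95% t interval for UCR versus conventional.

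| Shift | Residual SD 0.25 | Residual SD 0.5 | Residual SD 1.0 |
|---|---|---|---|
| 0 | 95.2% | 94.9% | 95.2% |
| 1 SD | 94.6% | 90.0% | 75.7% |
| 2 SD | 90.1% | 79.5% | 59.9% |

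UTR versus conventional stayed between 94.2% and 95.5% in every setting. UCR versus UTR behaves like UCR versus conventional by symmetry.

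**4. Bias on top of this.** If the model is also wrong in UCR by 0.5 SD, coverage at a 1 SD shift and residual SD 0.5 falls from 90.0% to 59.4%. That loss comes from the centre of the interval being misplaced, which a wider interval does not correct.

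**The case against.** The strongest reply has four parts.

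*The error may be negligible.* This stands as a limit on size. With no shift in the driver, coverage is about 95%, because shared error cancels. With a 1 SD shift and a well-fitting model it is 94.6%. The simulation is also a linear stand-in, not the two-pool model. A reader might infer that the UCR intervals are certainly too narrow. The documents do not show that. They show only that a source of error is left out whose size nobody has stated.

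*The method that fails in UCR is the collection, not the model.* This is correct. The article rules out subtracting one fixed fresh-dialysate concentration. It does not say that a two-pool model breaks down when dialysate sodium varies, nor that UCR patients' own data go unused. It would be too strong to say that the UCR p-values reflect only the model's structure.

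*Figures for false significance rest on an assumed bias.* With 20 per arm, a UCR bias of 0.25, 0.5 or 0.75 SD would be called significant in 12%, 34% or 64% of trials. Those are simply the power of a t test at those shifts. The documents give no such bias, and the figures say nothing about interval width. Nor does leaving out patient-level residual noise, by itself, bias the standard error of a mean when the model is right.

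*The full analysis plan may deal with it.* The article leaves derivation algorithms to that plan, so the absence of a described validation is not a finding. But the article itself fixes the calibration arms, the use of model output for all arms and the plain t test, and that test has no term for calibration error.

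**Conclusion.** The point holds in a limited form. The article sets a t test that treats calibrated model output as known, so its standard error omits calibration error. The omission is largely harmless for UTR versus conventional and may matter for both contrasts with UCR.

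Its size cannot be taken from the documents. With a calibration standard error of 0 to 0.316 between-patient SD in the contrast and 20 per arm, the real type I error runs from 5% to about 16%. This assumes that calibration error is roughly normal and independent of the spread between trial patients. The lower end applies if UCR sessions resemble the calibration sessions. UCR-specific model bias is a separate and unquantified risk.

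The analysis is secondary and exploratory, and the primary conclusion does not depend on it. The change is still worth making, because the Discussion gives this outcome first place among the secondary ones and describes as measured something that, in UCR, is estimated.

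**What to change.** 1. Keep model-based values in all three arms. For UCR versus conventional and UCR versus UTR, replace the plain t test by a bootstrap interval. Each replicate resamples the calibration patients and their sessions, refits the model, resamples the trial patients and recomputes the contrast.
2. Report the UCR results as model-based estimates that rest on an untested extrapolation to variable dialysate sodium. The bootstrap resamples only conventional and UTR calibration data, so it cannot reveal or allow for UCR-specific bias. The label is needed for that reason.
3. In the Discussion, let *measurement* refer only to the dialysate collections in the conventional and UTR arms.
4. Add the directly measured UTR versus conventional comparison as a supplementary analysis, not as a replacement. Only ten measured patients across both arms are guaranteed. If they split 5/5 (an assumption), 80% power needs a difference of about 2.0 SD, against 0.91 SD with 20 per arm.

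The cost is some extra analysis work and somewhat wider intervals for the UCR contrasts. No additional sampling is needed.

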(d). To assess if stricter volume control by conventional hemodialysis, UCR and/or UTR influences predialysis serum concentrations of (1) C-reactive protein, (2) D-dimer, (3) fibrinogen, (4) troponin T, and (5) N-terminal pro-B-type natriuretic peptide. These proteins are used as read-outs for inflammation (1, 2, 3), coagulation (2, 3), and cardiac function (4, 5) and are routinely determined at all three participating centers. The secondary outcome measure for objective (e), for example, the concentrations of the indicated laboratory parameters in both groups, UCR and UTR, at time zero and at the end of study phase 1, will be compared against the conventional hemodialysis group, and afterward against one another, using the two-sided Student’s *t* test. The individual change in these parameters, from time zero to the end of study phase 1, will be compared likewise.

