(e). To assess if stricter volume control in fluid-overloaded patients (using UCR, UTR or conventional hemodialysis) affects the concentration of various proteins that might serve as novel biomarkers (including high-density lipoprotein (HDL)-associated surfactant protein B; HDL-associated serum amyloid A; HDL-associated apoC-II; plasma tryptophan; plasma choline; plasma trimethylamine-N-oxide; and plasma endotoxin). We have recently discovered that various proteins, including those mentioned here above, may render HDL dysfunctional, in hemodialysis patients [44]. Especially with surfactant, we suspect an association with fluid overload. Moreover, plasma tryptophan, plasma choline, and plasma trimethylamine-N-oxide are markers of end-stage renal disease [45]. Since one or several of these proteins or molecules might serve as novel biomarkers, we would like to use the context of the present trial to establish diagnostic assays and analyze potential changes in the serum concentration of these proteins, before and after fluid removal. Endotoxin, found in the cell membranes of gram-negative bacteria, is a biomarker representing the gut flora. Endotoxin has been shown to be associated with inflammation, nutritional status and even mortality in hemodialysis patients [46]. An incremental rise in endotoxin levels has been shown along with the progression of chronic kidney disease, and especially initiation of hemodialysis [47]. It has been suggested that hemodialysis patients might have high endotoxin levels in the blood due to repeated bacterial translocation from the gut during hemodialysis, secondary to intradialytic changes in blood pressure and/or tissue perfusion. An association with chronic fluid overload has not yet been established, but might be suspected, as a consequence of higher ultrafiltration rates and thus decreased intradialytic stability. Here, we will measure endotoxin levels with an amebocyte limulus assay in all study patients, at time zero and at the end of study phase 1. The secondary outcome measure for objective (f), for example HDL-associated serum amyloid A in both groups, UCR and UTR, at time zero and at the end of study phase 1, will be compared against the conventional hemodialysis group, and afterward against one another, using the two-sided Student’s *t* test. The individual change in these parameters, from time zero to the end of study phase 1, will be compared likewise. The results of this secondary endpoint analysis will be published separately from the clinical results of the present study.

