
(f). To assess if stricter volume control in fluid-overloaded patients (using UCR, UTR or conventional hemodialysis) affects quality of life measures. The secondary outcome measures for objective (g) are the mental component summary (MCS) and physical component summary (PCS) derived from the Kidney Disease Quality of Life Short Form (KDQOL-SF^TM^) [48]. The scale of both summary scores is 0 to 100 (higher indicating better quality of life). MCS and PCS in both groups, UCR and UTR, at time zero and at the end of study phase 1, will be compared against the conventional hemodialysis group, and afterward against one another, using the two-sided Student’s *t* test. The individual change in these parameters, from time zero to the end of study phase 1, will be compared likewise.

(g). To demonstrate superiority of UCR and/or UTR over conventional hemodialysis in reducing dialysis complications when previously fluid-overloaded patients are entering phase 2 and phase 3 of the presented study. In study phases 2 and 3, patients either have to reduce their dry weight further, or else have to maintain their newly reached dry weight. The secondary outcome measures for objective (h) are potentially all of the items described here above, and will be compared against the conventional hemodialysis group, and afterward against one another, in the same fashion as described here above.

(h). To assess which hemodialysis treatment modality will be chosen by the patients at the end of the study. The choice of treatment will be compared as follows: (1) number of patients choosing UCR treatment against number of patients choosing conventional treatment; (2) number of patients choosing UTR treatment against number of patients choosing conventional treatment; (3) number of patients choosing UCR treatment against number of patients choosing UTR treatment. The statistical test for analyses (1), (2) and (3) will be the two-sided chi square test, for each analysis.

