#### Superiority definition

For all objectives listed, superiority will be assumed if a statistically significant difference between one group versus another group can be determined. The significance level (alpha) will be set at 0.05. With regard to the primary endpoint, according to our sample size calculation (see below), this study is suited to detect a minimal difference of 10% between groups, if the occurrence of intradialytic symptoms in the conventional group is similar as in a previous study [20].

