### Statistical analysis plan

The statistical analysis plan (SAP) provides full details regarding the analyses, the data display, and the algorithms to be used for data derivations. The SAP includes the definition of major and minor protocol deviations, which will be identified by medically trained staff before the study closure. Safety and tolerability are analyzed descriptively. Safety analysis is performed on the intention-to-treat (ITT) population. All secondary endpoint analyses are exploratory in nature.

Sample size calculation: for the primary endpoint analysis, we will assess the differences in intradialytic complications between the three study groups, only during the first study phase. Based on a typical occurrence of 0.14 dialysis-related complications per patient-day at risk in the conventional hemodialysis group [20], two-sided testing and an expected standard deviation of 10%, an alpha = 0.05 and a beta = 0.2, a sample size of 17 patients per group was determined to detect a minimum difference of 10% between groups. The UCR and UTR groups will be tested against the conventional hemodialysis control group, and afterward against one another. We expect a drop-out rate of approximately 10%. Individuals who do not complete the study cannot be replaced, because we do not include patients with hemodialysis vintage <3 months, and all patients who qualify for the study are asked to participate after the initial BCM measurement at all three centers. Thus, the study sample was determined to consist of 60 patients with ECW ≥15%, by BCM measurement. If patients are lost to follow-up, they will be excluded from the analysis

Two different analysis sets are defined for safety and efficacy, respectively. The efficacy of UCR and UTR will be assessed in all subjects who received the study method (at least once) and did not violate the protocol in a way that might affect the evaluation of the effect of the study method on the primary objective, that is, without major protocol violations. The per-protocol set is employed in the analysis of efficacy variables. The safety analysis set includes subjects who were randomized and received at least one study method (modified intention-to-treat). The safety set is employed in the analysis of tolerability and safety variables. Statistical analysis is performed with SAS.

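### Exploratory laboratory, biomarker and quality-of-life outcomes get three t tests per pair of arms with no main analysis named, and none uses the more precise adjustment for the time-zero value

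*Protocol article*

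**What the plan says.** All references are to the protocol article. Objectives carry the letters of the list in the section Objectives and outcome measures; the text under (d), (e) and (f) labels its own outcome measure one letter later.

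- Objective (d) covers five routine proteins. Objective (e) names seven candidate biomarkers, introduced as examples, so seven is a minimum. Objective (f) covers two quality-of-life summary scores.
- For (d) and (e), the values "at time zero and at the end of study phase 1, will be compared against the conventional hemodialysis group", then between the two regulated arms. For (f) the wording is parallel: "MCS and PCS in both groups, UCR and UTR, at time zero and at the end of study phase 1, will be compared". The test is a two-sided Student's t test throughout.
- All three objectives then add a third comparison: "The individual change in these parameters, from time zero to the end of study phase 1, will be compared likewise".
- Superiority definition: "For all objectives listed, superiority will be assumed if a statistically significant difference between one group versus another group can be determined". It continues: "The significance level (alpha) will be set at 0.05".
- Statistical analysis plan section: "All secondary endpoint analyses are exploratory in nature".
- Study setting and organizational details: time zero is the first session with dry weight reduction after the run-in, which follows randomisation. The run-in lasts up to 12 sessions for UCR and up to 6 for UTR; conventional hemodialysis has none (legend of Figure 1).

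No analysis adjusted for the time-zero value is mentioned, and none of the three tests is ranked above the others.

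**The concern.** Each outcome and pair of arms receives three p-values. The one at time zero precedes regulation and dry weight reduction, so it cannot reflect either. The end-value test ignores where each patient started. The change test subtracts the whole starting value, which is more correction than the data support whenever the correlation between the two time points is below 1.

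Two things are at stake. First, the end-value and change tests can disagree, and the plan has no rule for which stands, while the superiority definition accepts either. Second, precision is given away in a trial of 60 patients although the time-zero value is already collected.

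The protocol itself chooses these tests, so this concerns a stated method and not a detail left to an analysis plan that is not shown.

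**Working it through.** **The plan's own figure.** The only computed figure is the primary-endpoint sample size: difference 10%, SD 10%, two-sided alpha 0.05, power 0.80, 17 per group. The normal approximation gives 16; the exact t test gives 16.7, so 17 (power 80.7%). It reproduces. No SD, effect or correlation is given for the outcomes in (d) to (f), so those are assumed below.

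**Step 1: number of tests.** Measures × 3 forms (time zero, end, change) × 3 pairs.

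| Objective | Measures | All tests | At time zero |
|---|---|---|---|
| (d) | 5 | 5 × 3 × 3 = 45 | 15 |
| (e) | at least 7 | 7 × 3 × 3 = 63 | 21 |
| (f) | 2 | 2 × 3 × 3 = 18 | 6 |
| Total | at least 14 | 126 | 42 |

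One adjusted analysis per outcome leaves 14 × 3 = 42 contrasts.

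**Step 2: precision.** Assume the same SD at both times and correlation r between them. Take the variance of the end-value difference between two arms as 1.

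- Change: 2(1 − r)
- Adjusted for time zero: 1 − r²
- Adjusted relative to change: (1 − r²) / [2(1 − r)] = (1 + r)/2
- Adjusted relative to end value: 1 − r²

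| r (assumed) | Adjusted / change | Adjusted / end value |
|---|---|---|
| 0.3 | 0.65 | 0.91 |
| 0.5 | 0.75 | 0.75 |
| 0.7 | 0.85 | 0.51 |
| 0.9 | 0.95 | 0.19 |

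For any r strictly between 0 and 1 the adjusted analysis has the smallest variance, apart from the cost of one degree of freedom.

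**Step 3: behaviour of the tests.** Simulation of one outcome and one pair: 18 per arm (60 × 0.9 / 3), normal data, 40,000 trials per setting, time-zero differences due to chance only.

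No true effect, percentage of trials significant at 0.05:

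| r | End or change | Any of the three | Adjusted |
|---|---|---|---|
| 0.3 | 8.9 | 12.4 | 4.9 |
| 0.5 | 8.8 | 12.1 | 4.9 |
| 0.7 | 9.5 | 12.3 | 5.1 |
| 0.9 | 10.1 | 11.9 | 5.3 |

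Assumed effect of 0.8 SD, percentage of trials. End and change disagree in 2 × (either) − end − change:

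| r | End | Change | Either | Disagree | Adjusted |
|---|---|---|---|---|---|
| 0.3 | 64.7 | 50.4 | 73.7 | 32.3 | 67.5 |
| 0.5 | 64.2 | 64.4 | 80.2 | 31.8 | 75.3 |
| 0.7 | 64.8 | 85.3 | 91.5 | 32.9 | 89.7 |
| 0.9 | 64.4 | 99.9 | 100.0 | 35.7 | 99.9 |

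At this effect size the two planned tests give different answers on significance in about a third of trials.

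**The case against.** **Exploratory status.** All secondary analyses are called exploratory, (d) to (f) are worded as assessments and not as demonstrations of superiority, and the (e) results are to be published separately. This stands and lowers the weight. It does not remove the point, because the superiority definition applies its 0.05 rule to all listed objectives.

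**Time-zero comparisons are meaningless.** A reader might infer this from the usual argument against testing baseline differences between randomised groups. It does not fit here. The protocol defines baseline as the day of the bioimpedance measurement; time zero comes after randomisation and after run-ins of unequal length. A time-zero difference could therefore partly reflect the run-in, or losses before time zero, and is worth displaying. A display by arm serves that purpose without a test.

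**The planned tests are biased and the adjusted one is not.** The documents support neither half. Against a true pre-randomisation baseline the change-score t test is valid on average; its weaknesses are precision and sensitivity to imbalance. The proposed covariate is itself measured after randomisation, and efficacy is analysed per protocol with patients lost to follow-up excluded, so the usual guarantee for covariate adjustment does not carry over automatically.

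**Skewed markers are analysed untransformed.** This would also be an inference. The text mentions no transformation and does not say whether change is absolute or relative; such derivations are assigned to the SAP, which is not shown.

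**The within-patient question.** These objectives also ask whether stricter volume control, in any arm, alters the markers. Contrasts between arms do not answer that, so within-patient change keeps a descriptive place.

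**Conclusion.** The point holds as one of analysis choice for exploratory outcomes. Three t tests per outcome and pair are stated, none is primary, and any one can be read as superiority. Of at least 126 tests, 42 cannot show an effect of regulation or dry weight reduction. The other 84 are each less precise than an adjusted analysis. The gain over change runs from 35% less variance at r = 0.3 to 5% at r = 0.9; over the end value it runs from 9% to 81%. Accepting either the end or the change test raises the false-positive chance for one outcome and pair from 5% to about 9% to 10%.

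The direction does not depend on the assumed r, provided it lies strictly between 0 and 1; the size does. The simulated figures also assume normal data, 18 per arm, chance-only time-zero differences and, for power, an effect of 0.8 SD. The primary endpoint and its sample size are unaffected. The change should be made, but nothing in the trial's main conclusion hangs on it.

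**What to change.** For objectives (d), (e) and (f):

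1. Name one main between-arm analysis per outcome: a linear model of the end-of-phase-1 value on arm, time-zero value and centre (the stratification factor), reporting the three pairwise contrasts with 95% confidence intervals.
2. Show time-zero values by arm descriptively, without tests.
3. State that time zero follows randomisation and an arm-specific run-in (up to 12, up to 6 or no sessions), so a time-zero difference may not be chance alone and the contrasts are conditional on the value at that point.
4. Keep within-patient change as a descriptive display.
5. Reconcile the two descriptions of time zero, since its value becomes the covariate: objective (b) places it at the last session before the first reduction, the study-setting section at the first session with reduction.

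A log scale for skewed concentrations, with ratios of geometric means, is a suggestion for the SAP and not the correction of an error in the protocol.

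The cost is wording only. No new data or patients are needed, and the tests fall from at least 126 to 42 contrasts.
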